### **5.5 Benefit-Risk-Assessment**

Patients at risk of relapse after allogeneic stem cell transplantation will relapse in 100% without further treatment. In these cases the only chance of cure is a pre-emptive immunotherapy or a second allogeneic stem cell transplantation. The pre-emptive immunotherapy involves discontinuation of the immunosuppressive therapy and of donor lymphocyte infusions. The conventional donor lymphocytes doses are associated with a high risk of GvHD and therefore are limited in terms of the T cell dose. Thus the success of this treatment is less than 15%. Even the success of allogeneic stem cell transplantation is only at a maximum of 20%. Moreover, this approach is also associated with a high risk of morbidity and mortality.

The currently existing lack of sufficient data makes it difficult for us to identify all possible risks for the patients.

At present we estimate the GvHD risk of CIK cell infusion lower than the GvHD risk of DLIs. Due to the higher T-cell dose administered during CIK cell infusions, we expect a higher effectiveness than the above mentioned success rates of DLIs.

## **6 Safety Issues**

Monitoring and documentation of adverse events and adverse reactions.

Monitoring and documentation of serious adverse events and serious adverse reactions.

### **6.1 Definitions**

#### **Adverse Event (AE)**

An adverse event is any untoward medical occurrence in a patient or clinical trial subject administered a medicinal product and which does not necessarily have a causal relationship with this treatment. An adverse event can therefore be any unfavourable and unintended sign (including an abnormal laboratory finding, for example), symptom, or disease temporally associated with the use of a medicinal

product, whether or not considered related to the medicinal product. Pre-existing conditions, which worsen during a study, are to be reported as Adverse Events. They can become Serious Adverse Events if they fulfil one of the seriousness criteria described below.

All clinical adverse events (AEs) encountered during the clinical study will be reported on the AE page of the CRF.

#### Laboratory Test Abnormalities

Laboratory test value abnormalities as such should not be reported on the AE page of the CRF as adverse events unless in the investigator's opinion this abnormality is considered to be clinically significant. All clinically significant laboratory test value abnormalities will be reported on the AE page of the CRF as adverse events.

Within the scope of this study, considering the underlying disease and the post-transplant status, all laboratory test value abnormalities which regularly occur and which are expected will not be considered to be clinically relevant.

#### Adverse Reaction

Adverse reactions are all untoward and unintended responses to an investigational medicinal product related to any dose administered.

#### Serious Adverse Event (SAE) or Serious Adverse Reaction (SAR)

Any untoward medical occurrence or effect that at any dose- results in death

- is life-threatening
- requires hospitalisation or prolongation of existing hospitalisation
- results in persistent or significant disability or incapacity or
- is a congenital anomaly or birth defect

The definition and reporting requirements according to German Drug Law, GCP-V and ICH Guideline for Clinical Safety Data Management,

Definitions and Standards for Expedited Reporting, Topic E2 will be adhered to.

#### Suspected Unexpected Serious Adverse Reaction (SUSAR)

Any adverse reaction that is classified as serious and is suspected to be caused by the investigational medicinal product where the nature or severity of which is not consistent with the applicable product information (e.g. investigator's brochure for an unauthorised investigational product or summary of product characteristics for an authorised product).

To specify SUSARS within the scope of allogeneic stem cell transplantation:

Within the scope of allogeneic stem cell transplantation following cases of death have to be anticipated:

- Cases of death due to infections in the context of allogeneic stem cell transplantation
- Cases of death due to toxicity of the conditioning regime
- Cases of death as a result of recurrence of the underlying disease

## **6.2 Documentation and Reporting of serious adverse events**

Serious adverse events must be documented on the paper SAE-form. Documentation of SAE must be as complete and detailed as possible.

Toxicities are to be graded and documented on the respective reporting sheets, according to the Common Terminology Criteria for Adverse Events v4.0 (CTCAE; <http://ctep.cancer.gov>). All serious adverse events (SAEs) which occur in the concerned trial are subject of reporting using the SAE-form. This is independent of the fact whether the investigator acknowledges any causal relation between the event and the investigational medicinal product (IMP) (=SAR, serious adverse reaction). This includes type of event, start of the event, duration, seriousness and cause (if evident). Any SAE must be reported within 24 hours to the Sponsor.

The investigator has to report all SAEs (see exceptions below) by faxing the SAE form immediately (within 24 hours) to the authorized representative of the sponsor:

**Study Office -[contact]**

In case the required information is not available within the requested reporting window, follow up reports must be sent.

## **6.3 Documentation and reporting of suspected unexpected serious adverse reactions (SUSARS)**

According to GCP-V it is the responsibility of the sponsor to report all SUSARs that occur in this trial to the principal ethics committee, the principal governmental authority, all governmental authorities concerned

with the clinical trial and all involved investigators. Local regulations may require additional reporting e.g. to local ethics committee. According to German regulations the sponsor needs to send this report as soon as possible, but at its latest:

1. Within 7 days in case of a life threatening event or a lethal event. Within the following 8 days all further relevant information needs to be made available.
2. For all other events within 15 days.

According to the national German GCP-V §13(4) any event that will alter the current risk/benefit evaluation must be reported within 15 days to the principal ethics committee and to the competent authority.

## **6.4 Annual safety reports**

In addition to the expedited reporting, the sponsor or his authorized representative will submit, once a year throughout the clinical trial or on request a safety report to the competent authority and the Ethics Committee.

## **7 Ethics and General Study Administration**

This study will be conducted in compliance with the AMG, the German GCP-V, ICH GCP guidelines and/or other applicable ethical and regulatory requirements.

Investigators must have sufficient time to conduct the clinical study in compliance with the study protocol. Furthermore, they have to accurately and completely enter study data in the CRF. Investigators are responsible for obtaining informed consent of the patients as well as for the preparation and maintenance of adequate case files in order to record observations and other data relevant for this clinical study. Besides, they have to file the study-related records in the investigator site file (ISF) and have to maintain its actuality. They will permit study-related monitoring visits, audits by the sponsor or its representatives as well as inspections by regulatory authorities. The investigator must provide direct access to the study site's facilities, to source documents, and to all other study documents.

Sponsor of the study is the Goethe-University Frankfurt, represented by the President.

### **7.1 Ethical Aspects and Independent Ethics Committee (IEC)**

The Declaration of Helsinki (revision of 1996) is the accepted basis for clinical study ethics, and must be fully followed and respected by all engaged in research on human beings. Any exceptions must be justified and stated in the protocol.

The sponsor of the clinical trial has to submit all relevant study documents to the independent ethics committee (IEC) in charge, which for this study is the Ethics Committee of the Faculty of Medicine of the Goethe University Frankfurt (*central coordinator*). The study cannot be started unless a positive evaluation given by the ethics committee has been conveyed. Simultaneously to the central coordinator the local ethics committees (participating ethics committee) of the study centers will be informed about the planned study. The inclusion of new study centers has to be arranged by sending all relevant documents to the central coordinator and to the local ethics committee in charge at the same time. The study can be started in the new study center after the participating ethics committee in charge has validated the study center and the qualification of the investigator.

### **7.2 National Competent Authority (NCA)**

According to §§ 40-42 of the German drug law (AMG) it is the responsibility of the sponsor to obtain and maintain independent approval from the federal regulatory authority (BfArM/PEI).

The national German competent authority (NCA) for this clinical trial is the Paul-Ehrlich-Institute (PEI). An approval by the NCA must be available prior to study start.

### **7.3 Notification of the Study**

According to § 67 German drug law (AMG) the Sponsor is responsible to notify competent regional authority and the federal regulatory authority (BfArM/PEI) about the study and all principal investigators of the participating investigational sites. If no other agreements are made, the Sponsor will take over responsibility for investigator's obligation to report (§ 12 (3) GCP-V).

### **7.4 Insurance**

All patients of the clinical trial are covered by an insurance at the HDI–Gerling Versicherung AG. The patient / patient's parents will be explained the insurance coverage and conditions precedent and subsequent to the policy prior to the clinical trial. The patient/patient's parents will receive a copy of the insurance policy.

### **7.5 Financing**

Participating subjects of this study will not receive financial benefits.

### **7.6 Consent procedure**

#### **Patient Information and Informed Consent**

It is the responsibility of the investigator to obtain written informed consent from each patient participating in this study, after adequate explanation of aim, importance, anticipated benefits, and potential hazards and consequences of the study according to § 40 Abs 2 and § 40 Abs. 2a AMG. Written informed consent must be obtained before any study specific procedures are performed. For patients not qualified or incapable of giving legal consent, written consent must be obtained from the respective legal representative/ his/her guardians. It must be also explained to the patients that they are completely free to refuse to enter the study or to withdraw from it at any time for any reason without incurring any penalty or withholding of treatment on the part of the investigator.

The patient's guardians must give written consent prior to study participation. In case the patient is capable to understand her/his disease and the treatment concept of this study, she/he must be consented appropriately as an individual and give her/his consent separately.

By signing the consent form, the patient agrees with the "unwiderrufliche datenschutzrechtliche Einwilligung" according to § 40 Abs. 2a AMG. The patient also agrees to allow the monitor / auditor / health authorities to verify the collected patient data against the patient's original medical records for the purpose of source data verification.

The informed consent form personally signed and dated by the patient/ his/her guardians must be kept on file by the investigator(s), and documented in the case report form and the subject's medical records.

The investigator confirms obtaining the written informed consent to the sponsor.

## **7.7 Amendments**

Each amendment of essential study documents has to be approved and generated by the sponsor and LKP. Favorable opinion of IEC and approval of the NCA is required for substantial amendments prior to implementation.

## **7.8 Data Protection**

All study staff has to give due consideration to data protection and medical confidentiality. The collection, transfer, storage and analysis of personal study-related data are performed pseudonymized according to national regulations. The declaration of data protection is contained within the patient information/informed consent form.

## **8 Discontinuation or Early Termination of the Study**

### **8.1 Criteria for Discontinuation of the Treatment or Premature Withdrawal of the Patient**

Patients have the right to withdraw from the study at any time for any reason. The investigator also has the right to withdraw patients from the study in the event of intercurrent illness, adverse events, and treatment failure after a prescribed procedure, protocol violations, cure, administrative reasons or other reasons. Should a subject decide to withdraw, all efforts will be made to complete and report the observations as thoroughly as possible.

A complete final evaluation at the time of the patient's withdrawal should be made with an explanation of why the subject is withdrawing from the study. If the reason for removal of a subject from the study is an adverse event or an abnormal laboratory test result, the principal specific event or test will be recorded on the CRF.

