**The following criteria lead to stop of additional CIK cell infusions; patients are remaining in the study:**

- Development of GVHD > Grade II
- Response to CIK cell therapy: If mixed chimerism was the reason for study eligibility, than the achievement of complete donor chimerism leads to the stop of further CIK cell infusions. If the inclusion into the study was favored by minimal residual disease detection, the achievement of MRD negativity leads to a stop of additional CIK cell infusions.

- Severe infections

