**The following criteria lead to withdrawal from study; patients will be followed up for one month:**

- Pregnancy of female patients
- Relapse of the underlying disease during CIK cell treatment requiring other treatment (e.g. systemic chemotherapy, second stem cell transplantation)

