## Analysis

A descriptive statistics will be performed at the end of the study. An intent-to-treat principle (ITT) or per-protocol analysis will be done.

To analyze the efficacy of CIK cell treatment following factors will be considered:

- Complete and partial molecular response
- rate and duration of complete/partial molecular response following CIK cell administration at the end of CIK cell infusions and after 1 year of first CIK cell infusion
- rate of and time to non response
- rate of and time to relapse with previous partial/complete response
- Progression-Free survival (PFS) and overall survival (OS)
- Cumulative incidences of: haematological relapse/progression, deaths without relapse/progression
- Cumulative incidence of aGVHD > grade II and extensive chronic GvHD
- Median and range for the number of CIK cell dose and for cumulative dose CIK cells/kg for all patients, children and adults

- Median and range for cumulative T cells/kg according donor type (MSD, MUD,MMFD) that patient requires in the study

Complete molecular response is defined as the molecular remission: the Minimal Residual Disease not detectable (MRD < 10^-6) and Mixed Chimerism MC < 1%.

Partial response is defined as no molecular remission but not haematological relapse. Non response is defined as haematological relapse without previous or complete response.

The median of PFS and OS time will be estimated. Kaplan-Meier estimates will be used to estimate PFS probability and OS probability. Log-rank test will be used as appropriate. For PFS will be considered as events: disease progression or relapse, death without relapse/progression and secondary neoplasm. For OS death from any cause will be considered an event.

Gray-Model will be used for cumulative incidences. Patients lost to follow-up without event will be censored at the date of their last follow up evaluation.

PFS, OS and cumulative incidences will be estimated after 1 year initiation of CIK cell therapy and after 1 year until the last CIK cell infusion.

If the data meet the necessary requirements, longitudinal analysis will be conducted to explore the improvement of hematologic and immune reconstitution of leucocyte, CD3-, CD4-, CD8-, CD56-, and CD14-positive cells until the first year after begin of the CIK cells therapy.

The dynamic of cytokine profile during cell infusion and tumor escape mechanisms following CIK cell infusion will exhibit in curves over the time.

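### Section 8.1 does not separate the end of treatment from the end of follow-up, so later safety and survival data can be lost for reasons tied to outcome

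*Protocol*

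**What the plan says.** - **Section 8.1, opening text.** The investigator may, but need not, "withdraw patients from the study in the event of intercurrent illness, adverse events, and treatment failure after a prescribed procedure, protocol violations, cure, administrative reasons"; further unnamed reasons are allowed as well. For any withdrawal it asks: "A complete final evaluation at the time of the patient's withdrawal should be made". The undertaking to complete the observations is worded for the patient's own decision: "Should a subject decide to withdraw, all efforts will be made to complete and report the observations as thoroughly as possible". No such undertaking is given when the investigator decides.
- **Section 8.1, first list.** "The following criteria lead to stop of additional CIK cell infusions; patients are remaining in the study". It names GvHD above grade II, response (complete donor chimerism or MRD negativity, depending on the reason for entry) and severe infections. Section 3.3 gives patients who stop infusions but stay in the protocol 1 year of follow-up.
- **Section 8.1, second list.** Two grounds lead to withdrawal from the study with one month of follow-up: "Pregnancy of female patients", and relapse during CIK treatment that requires other treatment. Section 3.3 gives off-protocol patients 28 days.
- **Sections 2.3 and 2.4.** Primary endpoints are grade III or IV acute GvHD and extensive chronic GvHD. PFS and OS are due 1 year after the start and 1 year after the end of CIK therapy.
- **Section 11, Analysis.** "Patients lost to follow-up without event will be censored at the date of their last follow up evaluation". Duration of response, relapse after response and the cumulative incidence of extensive chronic GvHD are also to be analysed.
- **Section 6.1.** Serious adverse events include any occurrence that "is a congenital anomaly or birth defect".

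**The concern.** Several of the investigator's grounds for withdrawal are outcomes of the trial or lie close to them. Grade III GvHD is an adverse event and a primary endpoint. A severe infection is an adverse event or an intercurrent illness. Treatment failure overlaps with non-response. Cure is undefined and could be applied to a patient in molecular remission. Two investigators could therefore handle the same patient differently, one following for a year and one closing the record after a single evaluation, and both could cite Section 8.1.

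Kaplan-Meier and cumulative-incidence estimates assume that those who leave have the same later risk as those who stay. That assumption is doubtful if patients leave because of severe toxicity, remission or relapse. Section 11 also offers an intention-to-treat analysis, which needs data after treatment stops. No analysis plan can recover data that the protocol allowed sites not to collect.

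**Working it through.** **1. The plan's own precision figures.** Section 11 gives 95% interval widths of 0.318 (n = 40) and 0.448 (n = 20) at a rate of 0.4. The exact (Clopper-Pearson) limits are the Beta quantiles B(0.025; x, n−x+1) and B(0.975; x+1, n−x).

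- n = 40, x = 16: 0.249 to 0.567, width 0.318.
- n = 20, x = 8: 0.191 to 0.639, width 0.448.

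Both reproduce and are not disputed. They presuppose that every patient's status is known.

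**2. The rules side by side.**

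| Situation | Section 8.1, opening text | Section 8.1, lists, and Section 3.3 | Consistent? |
|---|---|---|---|
| GvHD above grade II | May be withdrawn (adverse event) | Stays in, 1 year | No |
| Severe infection | May be withdrawn (adverse event or intercurrent illness) | Stays in, 1 year | No |
| Response | May be withdrawn, if called cure | Stays in, 1 year | Unclear, as cure is undefined |
| Relapse needing other treatment | May be withdrawn (treatment failure) | Withdrawn; one month or 28 days | Yes on withdrawal, but short of the OS time points |

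**3. What each loss removes.**

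- After acute GvHD: the event itself is on record, because Section 8.1 requires an adverse event that causes removal to be entered on the CRF. Later extensive chronic GvHD, PFS and OS are lost.
- After a withdrawal labelled cure: response duration, relapse after response, PFS and OS are lost.
- After relapse: the relapse is known, so PFS is not the main loss; OS is.

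If the 4-6 week infusion interval is kept, a relapse during treatment falls at most 6 weeks after the last infusion. With 28 days (4 weeks) added, observation ends at most 6 + 4 = 10 weeks into the year after the last infusion. For OS 1 year after initiation, one month suffices only if relapse comes in month 11 or later (12 − 1 = 11).

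**4. Effect on a proportion.** With d known events and m patients of unknown later status among n, the proportion lies between d/n and (d + m)/n, a range of m/n.

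- m = 1: 1/20 = 5 points; 1/40 = 2.5 points.
- m = 4: 4/20 = 20 points; 4/40 = 10 points.

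This uncertainty comes on top of the tabulated interval widths.

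**5. Effect on 1-year OS of the relapse rule (illustration).** The protocol gives none of these rates, so all are assumptions: a fraction p relapses at 6 months; the death hazard is 0.1 per year without relapse and h per year after it; follow-up stops one month after relapse.

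- True OS = (1−p)·e^(−0.1) + p·e^(−0.05 − 0.5h)
- Expected Kaplan-Meier value = e^(−0.05) × [(1−p)·e^(−0.1/12) + p·e^(−h/12)] × e^(−0.1·(0.5 − 1/12))

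| p | h | True OS | Kaplan-Meier | Overstatement |
|---|---|---|---|---|
| 0.2 | 0.5 | 0.872 | 0.899 | 0.027 |
| 0.2 | 2.0 | 0.794 | 0.878 | 0.084 |
| 0.5 | 0.5 | 0.823 | 0.890 | 0.067 |
| 0.5 | 2.0 | 0.627 | 0.839 | 0.212 |

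Over this range 1-year OS is overstated by about 3 to 21 points. The whole of it comes from the mandatory relapse rule, not from the discretionary right.

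**The case against.** The best defence is that the opening text of Section 8.1 is a general permission, whereas the first list is specific and unconditional. A specific rule is usually read as governing the events it names, and Section 3.3 supports that with its 1-year follow-up. The protocol nowhere equates cure with molecular remission. An acute GvHD event that triggers withdrawal has already been counted. Censoring at last evaluation is standard. On pregnancy, Section 6.2 requires all serious adverse events in the trial to be reported, so a birth defect is not excluded from reporting.

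Much of this stands. The right is discretionary, so for adverse events and response the text permits outcome-related loss but does not show that it will happen. The specific-over-general reading is sensible, but no passage states it, and the opening text makes no exception for the listed events. The defence does not reach relapse, where short follow-up is the rule. Nor does it supply a step that would bring a birth defect to light: one month of follow-up would ordinarily end before birth.

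A reader might infer that the first list also keeps treatment failures in the study. It does not: relapse needing other treatment is in the withdrawal list.

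A reader might also scale up the sponsor's series in Section 1.5, adding 3/14 with grade III GvHD to 6/14 in continuing remission to reach 9/14 (64%) leaving follow-up. The documents rule that sum out. The three GvHD patients stayed in complete remission, so at most two of them (as the two who died in remission) can lie outside the six, and the union is at most 8/14 (57%). Nor is 6/14 (43%) a minimum: under a discretionary right the minimum is zero. The series also differs from this trial's population: 5 patients treated prophylactically, 3 in overt relapse, and 13 of 14 under 18.

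**Conclusion.** The point holds as a failure to separate stopping infusions from stopping observation. It has two parts of unequal strength.

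- **By rule:** after a relapse during treatment that requires other treatment, follow-up ends at one month or 28 days, against OS time points at 1 year. If mortality rises after relapse, which is an assumption here, the Kaplan-Meier estimate of OS is too high, by about 3 to 21 points under the rates illustrated.
- **By permission:** for adverse events and for whatever an investigator calls cure, observation may end with one evaluation, although the first list would keep overlapping patients for a year. Extensive chronic GvHD, PFS, OS and response duration can be biased. The direction is not fixed, since patients doing badly and patients doing well could both leave.

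The documents give no rate for either loss, so no forecast is possible; the firm figure is 5 points of best-to-worst-case range per patient at n = 20 and 2.5 at n = 40. That bias will occur through the discretionary right is not shown. The missing pregnancy outcome is a related gap in safety data, not an endpoint problem.

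**What to change.** Reconcile the opening text and both lists of Section 8.1 with Section 3.3, changing no treatment-stopping rule:

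1. State that the first list prevails over the investigator's general right for the events it names.
2. Delete cure as a ground for ending follow-up.
3. State that, whatever the reason infusions stop, relapse included, data collection ends early only on withdrawal of consent or loss to follow-up. GvHD, relapse and at least survival status are collected through the 1-year observational phase.
4. Replace the one-month and 28-day periods with that single follow-up rule, so that the sections agree.
5. Collect the outcome of any pregnancy up to birth.

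The cost is an amendment to the wording, longer follow-up of some patients, mostly on the three-monthly schedule already in Section 3.2, and one outcome form per pregnancy. For patients who have moved to other treatment, survival status alone would secure the OS analysis.
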